### Outcomes

Study results are assessed at baseline (week 0) and post-intervention (week 13). Outcomes are measured for all randomized participants, regardless of frequency or completion status. Participants who withdraw from the study at any time after randomization are invited to complete the final study assessments (12 weeks after the start of the intervention). Additionally, only the IG participants perform acute capillary blood glucose measurements before and immediately after an exercise session in the initial period of mesocycles 1, 2, and 4.

### Primary outcome

The primary outcome is the change in the HbA1c, evaluated through blood analysis. HbA1c was chosen as the primary outcome because of its importance in disease management. HbA1c is considered the gold standard in monitoring T2D, as it is a chronic measure and reflects the average blood glucose level over the previous 8 to 12 weeks [6]. Additionally, glycemic control, assessed by HbA1c levels, effectively reduces the risk of micro and macrovascular complications [41].

### Secondary outcomes

Clinically relevant secondary outcomes for individuals with T2D were established, including capillary blood glucose, systolic blood pressure (SBP), diastolic blood pressure (DBP), functional tests performance, depressive symptoms, diabetes-related emotional stress, sleep quality, and quality of life (QOL).

Capillary blood glucose is measured from blood samples collected from the participant’s fingertips. SBP and DBP are determined from office measurements. Capacity will be evaluated with the following tests: Arm Curl, 30 s-Chair Stand, Time Up and Go, 2 Minute Step Test, and Sit and Reach Flexibility Test. Depressive symptoms and diabetes-related emotional stress are measured using the Patient Health Questionnaire (PHQ-9) and the Brazilian version of the Problem Areas in Diabetes Scale (B-PAID). QOL and sleep quality will be measured using the EUROHIS-QOL 8-Item and Pittsburgh Sleep Quality Index Self-Report Questionnaire (PSQI).

### Other measures

Complementary measures of physical activity level, anthropometric data, eating habits, and subjective perception of well-being were assessed.

### Blinding

Blinding is applied to outcome assessors and data analysts of primary and secondary outcomes listed in this protocol. Due to the nature of the interventions, the team conducting the exercise sessions and the participants are not blinded. Participants are asked to withhold their assigned group and not talk about their interventions during outcome evaluations to ensure evaluator masking. In the event of unintentional uncovering for any reason, the researchers involved must notify the coordinator.

### Data collection

A single investigator carries out the home assessments pre- and post-intervention. During the assessments, he or she has a manual of standard operating procedures available. Two other researchers apply the online questionnaires. For this purpose, calls are made before to explain the procedures and immediately after the application to clarify doubts. In addition, the responsible investigator remains available to assist if any doubts arise during the completion of the questionnaire. All variables are assessed at baseline and after the intervention. Additionally, acute capillary blood glucose measurements are performed in the initial period of mesocycles 1, 2, and 4 and the subjective perception of well-being in week 13, both for the IG participants. The time scheme for study conduction is presented in Table 1.

**Table 1 Tab1:** Time scheme for RED study conduction

Study period										
	**Screening**	**Baseline and allocation**		**Post-allocation**					**Close out**	
**Timepoint**	**T0**	**T1**	Allocation	**T2**	12 weeks				**T3**	**T4**
		Baseline		Intervention start					Intervention end	Final evaluation
					Mesocycle 1	Mesocycle 2	Mesocycle 3	Mesocycle 4		
**Enrolment:**										
Eligibility screen	X									
Informed consent	X									
Randomization			X							
**Interventions:**										
Intervention group				X	X	X	X	X	X	
Control group										
**Assessments:**										
***Primary outcomes***										
Glycated hemoglobin		X								X
***Secondary outcomes***		X								
Capillary blood glucose		X			X	X		X		X
Blood pressure		X								X
Functional capacity		X								X
Quality of Life Questionnaire		X								X
Depressive Symptoms Questionnaire		X								X
Sleep Quality Questionnaire		X								X
Emotional stress related to diabetes questionnaire		X								X
Subjective perception of well-being										X
**Other measures:**										
Anthropometric assessment		X								X
Physical activity levels		X								X
Eating habits		X								X

### Measurement of the primary outcome

#### Glycated hemoglobin

Blood samples are collected in a specialized laboratory for the HbA1c levels analysis of each participant. Whole blood samples (2 mL) are collected from the antecubital vein of participants after 8 h of fasting. HbA1c levels are determined using a high-performance liquid chromatography method by a private laboratory.

### Measurements of secondary outcomes

#### Capillary blood glucose

Initially, participants will rest for 5 min, sitting in a chair with both feet on the floor and the back resting on the back of a chair. Capillary blood glucose will be measured from blood samples (0.6 μL of blood) collected from the fingertips, using disposable lancets and reagent strips (Accu-Check Guide, São Paulo). After collection, blood samples will be immediately analyzed by a portable glucometer (Accu-Check Guide, Roche, São Paulo, Brazil).

### Blood pressure

Office SBP and DBP measurements are obtained using an oscillometric BP monitor (HEM-7320, OMRON, China). The participant is kept at rest for 5 min; then, a measurement is performed on each arm, and then two more measurements are obtained on the arm with the highest value, always with a 1-min interval between measurements.

### Functional tests

The 30-s Chair-Stand test measures the strength of the lower limbs. Participants are instructed to sit and stand up from a chair 42 cm high from the seat, without the aid of the upper limbs, as many times as possible for 30 s [42].

The Arm Curl test is performed to check upper body strength. The test is performed holding a dumbbell in the dominant hand, with a load corresponding to 2 kg for women and 4 kg for men. Participants are instructed to perform the maximum number of elbow flexion repetitions in the full range of motion for 30 s [42].

The Time Up and Go (TUG) is used to measure agility and dynamic balance. The test starts with the participant sitting in a chair with a cone positioned 3 m away in front of them. Each participant is instructed to get up from their chair, walk as quickly as possible without running, go around the cone, and return to the starting position. The shortest time of two attempts is the test result. In addition, the test is also performed at the usual walking speed [43].

The 2-min step test is carried out to estimate the aerobic capacity. The test measures the maximum number of knee raises the individual can perform in 2 min. At the indicative signal, the participant starts stationary gait (without running), completing the maximum knee raises within 2 min. The minimum knee height is a midpoint between the patella and the anterior superior iliac spine. The evaluator counts the number of right knee raises [42].

Sit and Reach Flexibility Test is applied using the Wells bench, which measures the lower limbs’ flexibility. Participants must be barefoot, sit facing the base of the box with their legs extended and together, place one of their hands on top of the other, and then raise their arms vertically. When the evaluator gives the signal, the participant bends the body forward and reaches with the fingertips as much as possible on the graduated ruler without bending the knees or using rocking movements (insistence). Two trials are performed, and the lowest value is recorded [44].

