### Statistical analyses

Descriptive statistics will be used to describe the sample or data set characteristics by mean, standard deviation, 95% confidence interval, and absolute and relative frequency. Data normality will be tested by the Shapiro–Wilk test, and variances homogeneity of the will be tested by the Levene test. Primary and secondary outcome analyses will be conducted using analysis of covariance (ANCOVA), wherein baseline values will be considered as covariates. The intention to treat (ITT) analysis will include all randomized participants, with multiple imputations applied for missing data. Furthermore, a per-protocol (PP) analysis will be performed, including only participants with a frequency higher than 70% in IG and both time points measurements in both groups. Effect sizes between-group will be computed based on Cohen’s *d* and the 95% confidence interval. For the IG, acute capillary blood glucose will also be compared pre- and post-session throughout the intervention, using mixed linear models (2 × 3; session and time factors), followed by post hoc Bonferroni test. All data will be analyzed using SPSS version 22 at an alpha level of 0.05.

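### The sit-and-reach test asks for maximum reach but records the lower of two attempts, against its own instruction and the best-of-two rule used for TUG

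*Protocol article*

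**What the plan says.** The article lists sit-and-reach among the functional tests that form part of the secondary outcomes: "Arm Curl, 30 s-Chair Stand, Time Up and Go, 2 Minute Step Test, and Sit and Reach Flexibility Test" (Secondary outcomes). Under Functional tests, "Sit and Reach Flexibility Test is applied using the Wells bench", and the participant "reaches with the fingertips as much as possible on the graduated ruler". The scoring rule follows: "Two trials are performed, and the lowest value is recorded".

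TUG, described in the same section, also has two attempts. Its instruction is to "walk as quickly as possible without running", and its rule is "The shortest time of two attempts is the test result".

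The analysis is given under Statistical analyses: "Primary and secondary outcome analyses will be conducted using analysis of covariance (ANCOVA), wherein baseline values will be considered as covariates".

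**The concern.** On TUG a smaller number is a better performance, so keeping the smallest keeps the best attempt. On sit-and-reach a larger ruler reading is better, so keeping the smallest keeps the worst attempt. The two rules sound alike but work in opposite directions. As written, the sit-and-reach rule discards the maximum that the instruction asks for.

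Two things are at stake. The reported level of flexibility would lie below what participants showed and could not be compared with best-attempt scores. A reader also cannot tell whether the sentence states the rule actually used or a slip. If the rule were then applied differently at the two visits, the change from baseline would be distorted.

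**Working it through.** **Reading the text.** No figure in the article depends on this rule, so there is no stated number to reproduce.

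| | Sit-and-reach | TUG |
|---|---|---|
| Instruction | reach as far as possible | walk as fast as possible without running |
| Better performance | larger reading | shorter time |
| Attempts | 2 | 2 |
| Value kept | lowest | shortest |
| Attempt kept | worse | better |

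The table takes the ruler to run in the usual direction, with further reach giving a larger reading. The instruction supports this, and nothing in the article reverses the scale.

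**Size of the understatement.** The article gives no trial-to-trial variability. As an assumption, let the within-session SD be σ = 1, 2 or 3 cm, with two exchangeable normal attempts.

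- Expected gap between best and worst: 2σ/√π = 1.128σ, which is 1.13, 2.26 and 3.39 cm.
- The lowest attempt lies half of this, 0.564σ, below the person's own mean: 0.56, 1.13 and 1.69 cm. The highest lies the same distance above it.
- The SD of the lowest and of the highest about the person's mean is identical: σ√(1 − 1/π) = 0.826σ, or 0.83, 1.65 and 2.48 cm.

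A simulation of 1,000,000 participants gave the same gaps and SDs to within 0.01 cm.

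**Effect on the group comparison.** If σ is the same in both arms and at both visits, the lowest-value rule subtracts the same 0.564σ, on average, from every score. A common shift cancels in a between-group difference adjusted for baseline. Since the two rules have equal variance under this model, keeping the lowest costs no precision against keeping the highest.

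**When precision would suffer.** Suppose instead that each attempt falls short of true capacity by an exponential amount with mean 1, 2 or 3 cm (an assumption).

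| Mean shortfall (cm) | Lowest: understates capacity by | Highest: understates capacity by | Error SD, lowest | Error SD, highest |
|---|---|---|---|---|
| 1 | 1.5 | 0.5 | 1.1 | 0.5 |
| 2 | 3.0 | 1.0 | 2.2 | 1.0 |
| 3 | 4.5 | 1.5 | 3.4 | 1.5 |

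Here the lowest value is noisier, because it collects the failed attempts. The article does not say whether attempts behave this way.

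**The case against.** The strongest objection is that the rule does little to the trial's question. It applies equally in both arms and at both visits. One blinded assessor does the home assessments with a manual of operating procedures (Blinding; Data collection), and the analysis adjusts for baseline. This stands: under symmetric noise the treatment comparison is unbiased, and the 1.1 to 3.4 cm is a gap between attempts, not an error in the treatment effect.

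A reader might infer that the rule makes the outcome noisier and lowers power. The documents do not support that. It is false under the normal model and holds only under one-sided shortfalls. For example, if 10% of attempts fell 5 cm short, the lowest value would be affected in 1 − 0.9² = 19% of tests and the highest in 0.1² = 1%. The added variances would be 25 × 0.19 × 0.81 = 3.85 cm² and 25 × 0.01 × 0.99 = 0.25 cm². Both the 10% and the 5 cm are invented for illustration, and the article gives no residual variance to set the results against. A reader might also infer that the recorded attempt is often submaximal, or that the closing stretch in each session is meant to improve flexibility. The article states neither.

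It can also be said that sit-and-reach and TUG cite different sources, that the protocol sets no general best-of-two rule, and that the sentence may simply be a slip. The cited source is not available here, so whether the rule follows it cannot be settled. The conflict with the test's own instruction remains all the same. A slip in an explicit scoring rule still has to be corrected, because the sentence as printed defines the outcome.

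**Conclusion.** The point holds as a minor one. The stated rule scores the poorer attempt on a maximum-performance test, conflicts with the instruction that precedes it, and differs without explanation from the TUG rule beside it. It may be a wording slip for highest.

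If the rule was applied as written, recorded reach lies on average 1.13 within-session SDs below the best attempt shown, which is 1.1 to 3.4 cm for an SD of 1 to 3 cm. That range rests on an assumed SD and normal, exchangeable attempts. The group difference is not biased under symmetric noise of equal size in both arms and at both visits. A loss of precision is possible but cannot be established from the article. HbA1c, the sample size and the other outcomes are untouched.

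**What to change.** 1. Confirm from the operating procedures and source forms which value was actually recorded at baseline.
2. If the highest was recorded, correct the sentence and change nothing else.
3. If both attempts are on the source forms, enter both, analyse the highest at baseline and at week 13, and correct the sentence. Suggested wording: *Each participant makes two attempts; both readings are entered and the larger is the test result.*
4. If only the lower reading was kept at baseline, use the same rule at week 13 and state in the report that the score is the poorer attempt. Do not mix rules: lowest at baseline and highest at week 13 would add about 1.13σ of apparent improvement in both arms.

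Settle this before the analysis is unblinded. The cost is one sentence, a check of the forms and, if both attempts were kept, re-entry of one variable. No procedure is added for participants. Recruitment closed in June 2023, so whether step 3 is open depends on what was written down at baseline, which the article does not say.

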### Quality of life

QOL is measured using the EUROHIS-QOL 8-ITEM, an instrument validated for the Brazilian population [45]. The questionnaire consists of 8 items (general QOL, general health, energy, activity of daily living, self-esteem, social relationships, finances, and home). Each item is answered individually, using a Likert-type scale, from 1 to 5 points, ranging from “very bad to very good” (rating scale), “very dissatisfied to very satisfied” (satisfaction scale), and “not at all to extremely” (intensity scale). The total score ranges from 8 to 40 and indicates that the higher the score, the better the individual’s perception of their QOL.

### Depressive symptoms

Depressive symptoms are measured using the PHQ-9, an instrument validated for the Brazilian population [46]. It is a tool that aims to verify the presence of depressive symptoms in the last two weeks through a Likert-type scale from 0 to 3 points. It consists of nine questions with four response options ranging from “no, not one day” (0 points) to “almost every day” (3 points). The questionnaire also has the tenth question, referring to the interference of symptoms in daily life. In total, it is possible to have a score from 0 to 27, which indicates that the lower the score, the lower the depressive symptoms.

### Sleep quality

To measure sleep quality, the PSQI is used, an instrument validated for the Brazilian population [47]. The questionnaire includes 19 questions about the individual’s perception and five questions regarding the perception that the roommates of these individuals have about their sleep. If the participant does not have a roommate, the questions are not answered; therefore, they are not scored. These questions are grouped into seven components, with scores ranging from zero to three, where higher scores indicate worse sleep quality.

### Emotional stress related to diabetes

The B-PAID is used to analyze the emotional stress related to diabetes and the impact of diabetes and treatment on the lives of study participants. A 5-point Likert scale is used, ranging from “No problem = 0,” “Small problem = 1,” “Moderate problem = 2,” “Almost a serious problem = 3,” to “Serious problem = 4.” The B-PAID produces a total score that ranges from 0 to 100, where a high score indicates a high level of emotional distress. This total score is achieved by summing the 0–4 responses given on the 20 B-PAID items and multiplying this sum by 1.25 [48].

### Covariates

#### Anthropometric assessment

Body mass and height measurements are performed using a digital scale (HN-289, OMRON, China) and a compact stadiometer (MD, Brazil). From these data, the body mass index (BMI) will be calculated through the equation: BMI = body mass (kg)/height^2^ (m). Subsequently, the waist circumference is measured at the midpoint between the iliac crest and the last rib to verify the waist circumference/height ratio from these data***.***

### Physical activity levels

To measure the level of physical activity, the International Physical Activity Questionnaire—short version (IPAQ-C) is used in its short version, validated in its Brazilian version [49]. The IPAQ-C includes eight self-completion questions in different domains, such as work, leisure, domestic activities, and physical exercise. Data are expressed in minutes, and the metabolic equivalent is calculated (1 MET: 3.5 ml/kg/min). Like the other questionnaires, it is applied in electronic format, as already done in a previous study [50].

### Eating habits

The Food Frequency Questionnaire (FFQ) is used to control eating habits, as used in a previous study [51]. The questionnaire consists of a list of 16 foods prepared from previous studies [52, 53]. According to the Brazilian Food Guide Guidelines, these foods will be classified into two groups: in natura/minimally processed foods and processed or ultra-processed foods. Scores will be generated for these two food groups based on the frequency of consumption reported by the participants. The scores may vary from 0 to 32 points, in which higher scores represent better eating habits. A general healthy eating score will also be generated from the sum of all evaluated foods, which may vary from 0 to 64 points, where higher scores represent better eating habits.

### Adherence

For the IG participants, adherence measures are considered attendance and compliance in the intervention. Attendance is monitored through the online session’s frequency recording and treated as the percent of intervention sessions experienced by each participant, given the total number of applied sessions (thirty sessions). Compliance is treated as the percentage of intervention sessions performed without protocol deviations.

### Coordination and management of the trial

The coordinating center it is composed of the [name], responsible for supervising all phases of the study as the trial stages progress. The trial steering committee is made up of [name], MB, and VB and has the role of monitoring the study together with the coordinator center and supporting decisions. [name] is responsible for managing the study, recruiting, scheduling, logistically organizing home and laboratory evaluations, and carrying out home evaluations. [name] does part of data management. In addition, we have employees responsible for implementing the training program.

### Data management

Data collected in online forms are identified by subject identification and contain instructions for standard operating procedures. A specific lead researcher performs the check for missing or inaccurate data. Furthermore, data collected during the course of the research will be kept strictly confidential and accessed only by members of the trial coordination team. The participant’s identity is preserved and identified by the identification number (ID), and their details will be stored in a database to which only the coordination team will have access. If requested by the research coordination team, the anonymous study data may be shared with other researchers.

### Statistical analyses

Descriptive statistics will be used to describe the sample or data set characteristics by mean, standard deviation, 95% confidence interval, and absolute and relative frequency. Data normality will be tested by the Shapiro–Wilk test, and variances homogeneity of the will be tested by the Levene test. Primary and secondary outcome analyses will be conducted using analysis of covariance (ANCOVA), wherein baseline values will be considered as covariates. The intention to treat (ITT) analysis will include all randomized participants, with multiple imputations applied for missing data. Furthermore, a per-protocol (PP) analysis will be performed, including only participants with a frequency higher than 70% in IG and both time points measurements in both groups. Effect sizes between-group will be computed based on Cohen’s *d* and the 95% confidence interval. For the IG, acute capillary blood glucose will also be compared pre- and post-session throughout the intervention, using mixed linear models (2 × 3; session and time factors), followed by post hoc Bonferroni test. All data will be analyzed using SPSS version 22 at an alpha level of 0.05.

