### Randomization and allocation concealment

Once included in the study, the participant receives an internal number to be de-identified. The randomization sequence is stratified by sex and disease duration (< 5 years or ≥ 5 years) in blocks of different sizes with a 1:1 ratio in the Excel random function. The entire process of randomization and allocation into groups is carried out by an independent researcher not involved with the evaluations and intervention.

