### Sample size

The sample calculation was performed using the GPower version 3.9.1.4 program for *F* tests (considering two groups and two measurements), adopting a significance level of *α* = 0.05 and 80% power. Data for sample size calculation were extracted from the study results [32] for the primary outcome of HbA1c (effect size *f* = 0.24), resulting in a total n of 38 subjects. Additionally, twelve individuals (≈ 30%) will be included in the study due to the possibility of sample losses, totaling 50 participants randomized into the two groups.

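### The ANCOVA names only the baseline value and leaves out sex and disease duration, the two randomisation strata; if these are prognostic, the test is conservative and loses some power

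*Protocol article*

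**What the plan says.** Protocol article, Randomization and allocation concealment: "The randomization sequence is stratified by sex and disease duration (< 5 years or ≥ 5 years) in blocks of different sizes", and "with a 1:1 ratio in the Excel random function".

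Protocol article, Statistical analyses: "Primary and secondary outcome analyses will be conducted using analysis of covariance (ANCOVA), wherein baseline values will be considered as covariates". No other covariate is named there, and no other analysis model in the article contains sex or disease duration.

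Protocol article, Primary outcome: "The primary outcome is the change in the HbA1c, evaluated through blood analysis".

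Protocol article, Sample size: the calculation is "for *F* tests (considering two groups and two measurements"), "adopting a significance level of *α* = 0.05 and 80% power". It uses effect size f = 0.24 and gives 38 participants, raised by 12 to 50 for losses. It makes no use of the stratification factors.

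**The concern.** Stratified blocks balance the two groups on sex and disease duration. This takes the variation between strata out of the group comparison. A model without the strata still counts that variation as residual error. If the strata are prognostic, the reported standard error is then larger than the true sampling spread of the estimate: confidence intervals are too wide, the test rejects less often than 5% under the null, and the precision gained by stratifying is not used.

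At stake is some efficiency in a trial of 50, for HbA1c and for the secondary outcomes that share the model. The article specifies the model and its covariate, so the point concerns a stated choice that can be improved, not a detail left open.

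**Working it through.** **Inputs from the article.** Two strata factors, 1:1 allocation, α = 0.05, f = 0.24, 38 evaluable, 50 randomised.

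**Assumed inputs (not in the article).** Baseline-to-week-13 correlation ρ = 0.5; block sizes 2 and 4 (the article says only that sizes differ); the share R² of the baseline-adjusted residual variance that sex and duration explain together; a true difference of 0.70 SD.

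**1. The planned sample size reproduces.** For the group-by-time interaction with m = 2 measurements, λ = f²·N·m/(1 − ρ) = 0.0576 × 38 × 2/0.5 = 8.755, with 1 and 36 degrees of freedom. Power is 82.1%, and N = 38 is matched exactly, but only with ρ = 0.5 (ρ = 0.3 gives 50; ρ = 0.6 gives 30). The implied difference in change is f × √(8m) = 0.24 × 4 = 0.96 SD.

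**2. Mechanism.** In SD units, the residual variance after baseline is 1 − ρ² = 0.75. At N = 50 the baseline-only model reports SE ≈ √(0.75 × 4/50) = 0.245. With strata balanced exactly, the true spread is 0.245 × √(1 − R²). The real type I error is then P(|t₄₇| > 2.012/√(1 − R²)):

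- R² = 10%: 2.012/0.949 = 2.121, giving 3.9%.
- R² = 20%: 2.012/0.894 = 2.249, giving 2.9%.

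Simulation with real (sometimes incomplete) blocks agrees. Mean reported SE against true SD is 0.246 against 0.235 at 10%, and 0.247 against 0.226 at 20%. With both factors in the model, type I error stays at about 5%.

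**3. Power at 0.70 SD, N = 50.** This difference gives the baseline-only ANCOVA about 80% power: noncentrality 0.70/0.245 = 2.86. Ranges are across repeated simulations.

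| R² of strata | Type I error, baseline only | Power, baseline only | Power, both factors added | Loss |
|---|---|---|---|---|
| 0% | about 5% | 78.7% | 78.3% | none |
| 10% | 3.9–4.4% | 79.7–80.3% | 82.7–83.1% | about 3 points |
| 20% | 2.8–3.4% | 80.9–81.5% | 86.6–87.2% | about 6 points |

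With 5,000 runs, the simulation error of a 4% rejection rate is √(0.04 × 0.96/5000) = 0.3 points, so the type I figures are good only to about the nearest whole percent.

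**4. Power at the planning effect, 0.96 SD.** Baseline only against both factors added:

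| N | R² = 10% | R² = 20% |
|---|---|---|
| 50 | 97.1% vs 98.0% | 98.2% vs 98.8% |
| 38 | 91.8% vs 93.5% | 92.5% vs 95.7% |

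The loss here is under 1 point with all 50 analysed, and about 2 to 3 points with 38.

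**The case against.** **The harm is conditional.** The article gives no prognostic strength for sex or disease duration. What counts is what they explain after the outcome's own baseline value, which may already carry much of their effect. If they explain 5% or less, the loss is about 1 point or less; if nothing, there is none. This stands, and the point is worded accordingly. A reader might infer that the standard errors are certainly too large, but the documents do not show it.

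**The trial is not shown to be underpowered.** A reader might infer that power drops below plan. It does not follow. At the planning effect, with ρ = 0.5, the baseline-only ANCOVA has about 91% power even at N = 38, because ANCOVA is more efficient than the change-score comparison used for the sample size. The 0.70 SD difference is an illustration and is not in the article. This also stands.

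**A separate analysis plan may add the factors.** The article does not say that baseline is the sole covariate, so adding the strata would not contradict it. But it does write out the model and its covariate, so a narrow point about that model survives.

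**A reader might go further and see two competing covariate sets.** Anthropometry, physical activity and eating habits sit under a heading Covariates, and the article says "The Food Frequency Questionnaire (FFQ) is used to control eating habits". One might fear that their week-13 values will be adjusted for, removing part of the exercise effect. The documents do not support this. The heading belongs to the measurement section, Other measures and Table 1 class the same items as complementary, and no sentence puts any of them into a model.

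**Conclusion.** The point holds as an efficiency improvement. Randomisation uses sex and disease duration; the stated ANCOVA does not. If these factors predict the outcome beyond its baseline value, the stated model is conservative: under the assumptions above, at 50 participants and 0.70 SD, type I error is about 4% and 3% and the power loss about 3 and 6 points for R² of 10% and 20%. With non-prognostic factors there is essentially no loss, and at the 0.96 SD implied by the sample size calculation it is about 3 points at most.

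The direction is firm whenever the factors matter. The size is not, because it rests on the assumed R², correlation, block sizes and true difference. The treatment estimate is not biased and false positives are not made more likely.

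**What to change.** In Statistical analyses, define the model for the primary and all secondary outcomes as: *ANCOVA with group, baseline value of the outcome, sex and disease-duration stratum (< 5 / ≥ 5 years)*. Record the change in the analysis plan and the registry before group-level results are seen; the article says that data analysts are blinded.

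The cost is one sentence and two residual degrees of freedom (47 to 45 with 50 analysed). Both variables must be known for every participant in order to randomise, so no new data are needed. If the factors turn out to explain nothing, the price is about 0.4 points of power (78.7% against 78.3%), which is within simulation error.
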